**Fig. 1 Fig1:**
[figure not shown]
Multi-level influences on Multiple Family Group (MFG) implementation and child outcomes

Thus, in this paper, we present and describe in detail a protocol for a scale-up longitudinal experimental study that uses a mixed-methods, hybrid type II, effectiveness implementation design [81] to test the effectiveness of an EBP, called the Multiple Family Group (MFG) family strengthening intervention, aimed at improving child disruptive behavioral challenges in Uganda while concurrently examining implementation – specifically, the multi-level factors that influence uptake, implementation, sustainment, and youth outcomes. In summary, the objective of the proposed study is to examine the implementation and outcomes associated with an EBP, specifically MFG targeting youth disruptive behavior challenges and success, through a scale-up intervention study in Uganda (see https://sites.wustl.edu/smartafrica/ for more details about the SMART Africa Center). More specifically, the study objectives are:To examine short-term and longitudinal outcomes associated with the MFG (disruptive child behavior, behavioral functioning)To compare the uptake and implementation of MFGs by trained existing family peers and CHWsTo elucidate multi-level factors that influences uptake, implementation and youth outcomes

## Methods

The proposed study will be conducted across primary schools representing both semi-urban and rural communities. We expect to involve 3000 youths (in primary schools grades 2 through 7; 8 to 13 years) and their adult caregivers (3000) in Uganda. Schools will be randomly assigned to three study conditions: (1) MFG delivered by trained family peers; (2) MFG delivered by CHWs; or, (3) comparison: mental health materials. Data will be collected at baseline, 8 and 16 weeks, and 6-month follow-up (10 months from baseline; see Fig. 2 for the Standard Protocol Items: Recommendations for Interventional Trials (SPIRIT) schedule of enrollment, interventions, and assessments). A SPIRIT checklist (see Additional file 1) has also been included for further details on the study protocol.

**Fig. 2 Fig2:**
[figure not shown]
Standard Protocol Items; Recommendations for Interventional Trials (SPIRIT) schedule of enrollment, interventions, and assessments

### Study setting

The proposed study will target youth attending primary schools in Rakai District and the greater Masaka region (southwestern Uganda) as well as their caregivers. The region is heavily affected by poverty with high HIV prevalence rates (at least 8.5% vs. 6.5% found in the national average) [82]. The area also has large number of children with no living biological father, mother or both (also known as orphaned children). An estimated two in five children are orphaned to AIDS each year in these districts [82].

### Study population, recruitment, and retention

#### Sampling and recruitment

##### Schools

The study involves the active collaboration of the Masaka Diocese which operates slightly over 420 public primary schools in Rakai District and the greater Masaka region. We will recruit medium-sized schools to participate in the study. All schools with a total enrollment of more than 900 students will be eliminated as they are considered above average enrollment. Similarly, all schools with a total enrollment of less than 350 students will be dropped because they are considered below the average normal enrollment of at least 50 students per grade. Schools that remain on the list after this stratification will be contacted to schedule informational meetings with the school leadership and staff (school heads/directors, head teachers, and teachers) to present the research study and gauge interest in study participation. Follow-up meetings will be scheduled when necessary. The research team will compile a list of the schools that express commitment to participating in the study (see the “Randomization” section for further details).

##### Children and caregivers

Schools will be asked to organize meetings for all families to learn about the study. All research staff will be on hand at each meeting to provide the opportunity for parents to ask questions about the study individually or as part of a larger group of parents. If parents and children are interested in participating, each of them will have an opportunity to meet individually with research staff and provide informed consent and child assent.

Following consent procedures, parents will be asked to complete screening tools for child DBDs (see Table 3). The screening will be conducted by project coordinators and research assistants. If the child meets the criteria for a clinically meaningful behavioral problem on any of the screening measures, they will be considered “positive”. They and their caregivers will be invited to enroll in the study and an appointment to complete a full baseline assessment (for both child and caregiver; see the “Measures” section) will be made prior to beginning to attend MFG meetings. If a child does not evidence a DBD, they will be considered “negative.” The family will be enrolled to attend the MFG meetings (all families in the school community will have the opportunity to attend to decrease stigma, but also enhance functioning of all parents/families). An appointment to complete a shortened version of the baseline assessment (for both child and caregiver; see the “Measures” section) will be made prior to beginning to attend MFG meetings. The child and the caregiver will be monitored at each time point with shortened versions of the assessment batteries. If at any point during these assessments, the child meets criteria for DBD, both the child and the caregiver will complete full version of the assessment batteries.

School meetings is the first way that we will reach out to parents of children enrolled in the potential schools. Research staff will also conduct home visits (as has been typically done in other studies in the area). In total, we will recruit 3000 children and their adult caregivers across three study conditions. We will continuously monitor study participants’ recruitment and enrollment during weekly staff meetings to ensure equivalent involvement across conditions by: gender of youth, age and adjust if imbalance occurs accordingly.

##### Parent peers and CHWs to facilitate the adapted MFG

At each of the school sites assigned to the parent-peer-delivered condition (*n* = 10), the head of school and the Chair of the Parents Teachers Association (PTA) will identify up to six parent peers to receive the training to deliver the adapted MFG. Parent peers will have already received some training for their current roles (e.g., workshops in methods to reach out to parents whose children are not performing well in school or not attending; facilitation skills in relation to organizing parent meetings). We expect to recruit 60 parent peers from the 10 schools in the parent-delivered condition.

At each of the school sites assigned to the CHW-delivered condition (*n* = 10), we will collaborate with the village local leaders, the district health officials, and the Ministry of Health (MOH) to identify up to 60 existing outreach workers associated with local primary care clinics in the study area. CHWs have already received training in health assessment, home and school outreach and facilitation of health-related meetings. Many of the CHWs are also local leaders within their communities. We expect to recruit 60 community health outreach workers to deliver the adapted MFG to children from 10 schools assigned to their condition.

##### Inclusion/exclusion criteria

Inclusion criteria are as follows: (1) school head teacher willing to participate; (2) parent peers or CHWs willing to participate; (3) adult caregiver of a child in primary 2 through 7, 8 to 13 years, willing to consent and available for research and intervention activities; (4) a child screened for oppositional defiant disorder (ODD) or conduct disorder (CD) and willing to assent. Exclusion criteria include lack of understanding of the study and participant rights and refusal to participate. If the youth or adult caregiver presents with emergency needs (e.g., hospitalization), needed care will be secured, rather than study participation.

#### Sample attrition and retention

We believe that attrition will be minimal because the investigative team is known in the schools and communities, and has substantial experience recruiting and tracking “hard to reach” families. The study will take place in a highly stable region of Uganda, where geographical moves are rare. Using the same protocols that we have used in our prior studies, we will ask the participants to give their postal box number and telephone number (if they have one), and names, addresses, and contact information for three people who will always know how to reach them. Participants will be reminded that if we are to contact the people listed, we would never discuss any details about their involvement in the study. We will use these records to track the location of study participants over time. We have effectively used these methods in other research programs, resulting in very low attrition rates (for SUUBI-Uganda, 2.4% at 10-month follow-up and 7.3% at 24-month follow-up; Suubi+Adherence, 4.3% at 48 months, and Bridges, 4.1% at 12 months, 9.3% at 48 months) [10–13, 65–71]. Hence, we expect attrition from baseline to the end of follow-up to be no more than 20%. We will keep careful records for those who drop out of the study and test for attrition bias based on data that we will have prior to study dropout. To the extent that such bias is present, we will limit generalizations accordingly, or where possible, introduce statistical adjustments (hot deck imputation methods [83–86] to complete missing observations, and thus to address bias.

#### Statistical power calculations

The present research uses multi-level structural equation modeling (MSEM) as opposed to traditional multi-level modeling (MLM) because of the presence of mediation [87]. The two are closely related, but the former is primarily available in the Mplus computer software. Power computations in MSEM models are complex because of the large number of assumptions about population parameters that must be made [87–89]. One approach is to power the study based on limited information estimation strategies that focuses on the most sample size demanding equation in the broader system of equations [90]. For longitudinal MLM studies, this also requires taking into account the potential presence of correlated errors of measurements, person-specific effects, and dropout [91–95]. Hedeker and Gibbons [96] also provide a power analysis approach that allows for specification of anticipated attrition patterns and correlations among the repeated observations. Power analyses for a linear trend over time take into account: (1) four measurement time points; (2) a three-group design; (3) a random effect for time and a random effect for facilitator within school for provider-type hypotheses; (4) a residual autocorrelation of rho = .3 and; and (5) an 8% attrition rate between successive time points. Randomization is at the school level. For the hypotheses involving children nested within facilitators or schools, our sample size calculations also incorporate recommendations outlined in Donner et al. [97], and allow for an inflation factor such that our effective sample size is two thirds that of the actual sample size. Table 1 presents detectable effect size (a between group difference increasing linearly from 0 at baseline to effect size measured in standard deviation (SD) units at the last time point) corresponding to 80% power.

**Table 1 Tab1:** Power analysis

Unit (*n* per group)	4 time points	Effect size
School (*n* = 30)	0.39	moderate
Facilitators (*n* = 120)	0.28	moderate
Family (*n* = 3000)	0.10	small

### Study conditions

#### Treatment arms

The MFG platform for EBP delivery is a series of weekly meetings guided by a protocol [56, 60, 75]. Groups are held weekly and are facilitated by trained and supervised group leaders (in this case either parent peers or community health outreach workers). Groups can consist of up to 20 families involving adult caregivers and all children over 6 years of age in the family [74, 75, 98]. MFG targets, family skills, and goals for the manual to be used in Uganda—adapted from the 4Rs and 2Ss in the US, CHAMP South Africa and Suubi+Maka (Uganda)—are summarized in Table 2.

**Table 2 Tab2:** Multiple Family Group (MFG) targets, family skills, and goals

MFG target	Empirically supported family skill	MFG goals
*R*ules	Family organization; consistent discipline	Clarify rules, consequences, rewards
*R*esponsibility	Inter-connectedness; expectancies	Clarify responsibilities, expectations, rewards
*R*elationships	Family warmth; within-family support	Schedule for positive family interaction
*R*espectful communication	Family communication; family conflict	Listening/ talking skills (parents/children)
*S*tress	Parenting hassles and stress; life events	Identify stressors undermining family change
*S*ocial support	Social isolation	Within-family and external support plan

#### Description of MFG intervention protocol

The protocols have been designed to provide multiple opportunities during each session to directly apply content to the realities of family life, emergent cultural and values perspectives, as well as to tailor messages to age of child. We have built in redundancy for missed appointments and opportunities for reinforcement. We aim for families to attend at least seven to eight meetings, as findings suggest that this dose is needed for reductions in child behavioral difficulties and prior studies in the US and SA suggest that most families will reach this goal [57, 58].

#### Program delivery

We will train at least six facilitators per school site to deliver the MFGs in both MFG-parent-peer-delivered and MFG-CHW-delivered condition. Training for parent peers and CHWs will occur separately, by condition. Incentives to participate and complete training will include: receiving certification in child mental health competency to be offered by the local district leaders—including the LC5 Chairperson and the district health official, and transport facilitation needed to complete project tasks and a community-wide recognition event thanking facilitators for their contributions.

#### Training and supervision

Training will consist of up to six modules. Training focuses on childhood conduct difficulties, family-level factors that have been linked to child outcomes, strategies to enhance engagement and motivation, and group facilitation skills and processes specific to MFGs. At the end of the MFG training, we will administer a Knowledge and Skills Assessment Test (KSAT), to assess mastery of the content (live competence demonstrations and knowledge questions read aloud to facilitators). The criteria of mastery for the KSAT will be set at 85%. During the MFG implementation period, facilitators will receive 2 h per month of group supervision across sites while the MFGs are in progress.

#### Description of the comparison condition

Mental health wellness materials from the MOH will be made available to all children and families recruited in the study (across all the three study conditions). We will adapt printed materials on child mental health based on those recently created by the MOH.

#### Adaptation of MFG manual

During phase I (months 1 to 12), the study team will review the existing MFG intervention protocol, as well as the South African training and delivery methods used in the CHAMP program of research (e.g., cartoon format of information delivery and family practice activities, training protocols for lay counselors and community facilitators), and the SUUBI family economic strengthening approach. Further, these working groups will review the existing evidence related to the relationship between specific parent management practices, family organizational processes and livelihood approaches, and positive youth behavioral outcomes in order to align with perspectives and organization of families in SSA. The intervention adaptation team will comprise the in-country research team as well as community stakeholder volunteers (one to two teachers, one to two parents, one to two CHWs) recruited to assist with intervention adaptation.

In the Ugandan context, faith-based institutions, including the church and religious leaders, are longstanding partners to the investigative team. The same guidelines for partnerships that organize our work with local, regional and national policy-makers, and non-governmental organizations (NGOs) also guide our intensive collaboration with religious, cultural, and community leaders. These partnerships are characterized by intensive, ongoing involvement and communication with substantial effort invested in developing shared goals, understanding and feedback processes across the entire span of the project and country contexts.

The adaptation process will follow steps previously outlined by Petersen and McKay [40, 61, 75]. Specifically, interaction between in-country and cross-country teams will be intensive and systematic. Team members will identify core elements of the existing science on parenting and family life that need to be addressed within each country context (for example, in prior studies set in SA, rapid ethnographic studies were conducted to identify elements of family life that were missing from existing evidence-based, particularly perceptions of disempowerment of parents, harsh discipline strategies, parents’ and children’s rights) and incorporate evidence-informed intervention elements into the adapted MFG intervention and training protocols.

### Randomization

Stratified cluster randomization of schools to conditions will be used, with schools stratified into four strata based on two variables: (1) student population size (medium size vs. large) and; (2) geographical location (rural vs. semi-urban), to ensure balance on those variables. The restricted randomization technique of Hayes and Moulton [99] will be used to assure overall school balance across the three experimental groups. Each school will be randomly assigned to one of the three study conditions such that all selected children from a particular school will receive the same intervention (reduce contamination). These schools are geographically apart, with limited transportation. Hence, the risk for contamination will be minimal (See the “Contamination” section).

Specifically, to select and randomize the potential schools, we will follow the following procedure:A list of the primary schools in the area will be obtained from the Masaka Diocese that oversees all the 420 church-founded but government-supported public primary schools in the Rakai District and Masaka regions; and the District Education OfficeAll schools with a total enrollment of more than 900 students will be eliminated as they are considered above average enrollment. Similarly, all schools with a total enrollment of less than 350 students will be dropped because they are considered below the average normal enrollment of at least 50 students per gradeSchools that remain on the list after this stratification will be contacted to schedule informational meetings with the school leadership and staff (school head teachers, and teachers) to present the research study and gauge interest in the study. During these meetings, the purpose of the study will be explained and what the school’s participation entails will be laid out. All study-related questions will be answered. Follow-up meetings will be scheduled when necessaryThe research team will compile a list of the schools that express commitment to participating in the studyThirty schools from this list will be randomly chosenUsing SPSS software version 24, each of these 30 schools will be randomly assigned to one of the three study conditions, i.e., 10 to the adapted MFG delivered by parent peers; 10 to the adapted MFG delivered by CHWs; and 10 to the comparison condition

We estimate that a total of 30 schools will allow us to identify sufficient number of youth and nest them within trained program facilitators. This will allow the research team to detect a small to moderate effect based upon power calculations. Thirty schools is our best estimate of the total student population needed to draw a sufficient sample. The number of schools will be adjusted if needed.

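### Schools are stratified as medium versus large although only medium-sized schools are eligible, and the allocation steps name neither strata nor restriction, so balance is not assured as written

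*Protocol article*

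**What the plan says.** In the protocol article, the Randomization section opens with stratified cluster randomization, "with schools stratified into four strata based on two variables". The first is "student population size (medium size vs. large"; the second is "geographical location (rural vs. semi-urban), to ensure balance on those variables". It then adds: "The restricted randomization technique of Hayes and Moulton [99] will be used to assure overall school balance across the three experimental groups".

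Eligibility of schools appears twice. The Schools section states: "We will recruit medium-sized schools to participate in the study". It continues: "All schools with a total enrollment of more than 900 students will be eliminated as they are considered above average enrollment". The lower limit is that "all schools with a total enrollment of less than 350 students will be dropped". The step list in Randomization repeats both limits.

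That step list is presented as the specific procedure for selecting and randomizing schools. Thirty schools are drawn at random from those that commit to take part. Then, with SPSS, "each of these 30 schools will be randomly assigned to one of the three study conditions", 10 to each. The steps use the word stratification once, for the enrolment screen.

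**The concern.** A stratification factor works only if eligible schools fall on both of its levels. Here the eligibility text describes the whole retained range as medium-sized, while the stratification text splits schools into medium and large. Someone running the allocation could not tell which schools belong in the large stratum.

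The second difficulty is that the most operational text in the section, the step list, says nothing of strata or a restricted set. A person working from the steps alone could produce an unstratified 10/10/10 allocation and believe the protocol had been followed. With only 10 schools per arm, chance imbalance in a school characteristic can be sizeable, and size and location are the two characteristics that the protocol says it will balance.

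**Working it through.** **Step 1: the stated counts.** Two binary factors give 2 × 2 = 4 strata, and 3 arms × 10 schools = 30 schools. Both agree with the article. The lower limit is also coherent: 350 pupils / 50 per grade = 7 grades.

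**Step 2: the strata after eligibility.** Retained schools have 350 to 900 pupils and are described as medium-sized. Schools above 900 are removed. No cut-off inside 350 to 900 is stated. Size, as labelled, then has one level: 1 × 2 = 2 usable strata.

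**Step 3: the step list against the opening.**

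| Element | Opening of Randomization | Step list |
|---|---|---|
| Four strata (size × location) | yes | not mentioned |
| Restricted randomization | yes, balance criteria not listed | not mentioned |
| Draw of 30 schools | – | random, from the committed list |
| Assignment | by stratum, with restriction | random, 10/10/10, SPSS |

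The steps are silent on the strata. They do not say that allocation is unstratified.

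**Step 4: what a literal reading of the steps would allow.** Suppose the 10/10/10 assignment is made with no strata and no restriction, and K of the 30 schools are rural. The article does not give K, so it is an assumption and is varied. The probability that the three arms receive x, y and w rural schools (x + y + w = K) is

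C(10,x) · C(10,y) · C(10,w) / C(30,K).

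Sum this over all allocations in which the largest and smallest arm counts differ by at least 3 (or at least 4). For K = 15, C(30,15) = 155,117,520, and the products with a gap of 3 or more add to 72,435,312, so the probability is 72,435,312 / 155,117,520 = 0.467. For K = 6 it is 178,650 / 593,775 = 0.301.

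| Rural schools K (assumed) | P(gap ≥ 3) | P(gap ≥ 4) |
|---|---|---|
| 6 | 0.30 | 0.12 |
| 9 | 0.40 | 0.20 |
| 12 | 0.45 | 0.25 |
| 15 | 0.47 | 0.26 |
| 18 | 0.45 | 0.25 |
| 20 | 0.50 | 0.23 |

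The values do not rise smoothly, because a K that is not a multiple of 3 cannot be split evenly. Applying the same formula to every K from 6 to 20 gives at most 0.53 for a gap of 3 or more and 0.27 for a gap of 4 or more (both at K = 14 and K = 16). More lopsided splits give less: at K = 3, P(gap ≥ 3) = 3 × C(10,3) / C(30,3) = 360 / 4,060 = 0.09, and a gap of 4 is impossible.

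**Step 5: comparison.** Assignment balanced within location strata holds the gap to at most one school per stratum. No similar figure can be given for size, because the article gives neither a cut nor a distribution of enrolment.

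**The case against.** The strongest reply is that the section commits, before the steps begin, to stratified allocation on both factors and to restricted randomization. A short list that names the software and the totals does not cancel those commitments, and an allocation that is stratified and restricted can end in 10/10/10 and be run in SPSS. This stands. A reader might infer that the promised balance is not delivered, or that the descriptions cannot all be followed. The documents do not support either reading: the steps omit the strata without contradicting them, and balancing on rural versus semi-urban can be carried out as stated. The probabilities above describe only what would follow if the opening commitments were ignored.

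It can also be said that large may mean the upper part of 350 to 900, with the cut-off and restriction criteria left to a full protocol that is not shown. Leaving a number to the full document is acceptable. But the article does not say that large has this meaning, and its own label for the whole retained range is medium-sized. The clash of labels is in the text at hand.

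Finally, the data analysis plan compares schools across conditions at baseline and adjusts for covariates that differentiate the groups. That offers a route to repair a chance imbalance, so the consequence is partly covered. The route depends on what the baseline data show, however, and does not name location or enrolment. School dummy codes in the Aim 1 models are optional.

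**Conclusion.** The point holds as a defect in how allocation is specified. As labelled, the size factor has one level among eligible schools, and the stated four strata reduce to two. The step list does not carry the promised strata or restriction, so balance on size and location is not assured as written. It does not follow that balance will fail.

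If the steps were followed literally, a difference of 3 or more rural schools between two arms of 10 would have a probability of about 0.30 to 0.50 (up to 0.53 at some intermediate splits). That figure assumes 6 to 20 rural schools in 30, which the article does not state, and it covers location only. The trial is not invalidated, but its allocation cannot be reproduced from the text, and correction is worthwhile because it is cheap.

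**What to change.** 1. Define the size stratum by a cut within 350 to 900 pupils, for example the median enrolment of the committed schools, or drop size as a stratification factor and state two strata.
2. In the allocation step, state that the 10/10/10 assignment is made within those strata and from the restricted set.
3. The Trial status section reports recruitment and baseline assessment under way, so schools may already be allocated. If so, report the procedure actually used, including whether strata and restriction were applied.
4. In either case, prespecify location and enrolment as school-level covariates in the Aim 1 models, instead of adjusting only for covariates found to differ between arms.

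Items 1 to 3 cost wording only. Item 4 uses two school characteristics that are obtainable before allocation. With 30 schools and 3 arms there are about 30 − 3 = 27 school-level degrees of freedom; two covariates leave about 25.
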